### Resource use/costs

The cost components for this complex natural experiment involve integrating multiple NTE components, from differing perspectives, that could be affected by the policy changes in Aberdeen and Glasgow. There are multiple resource use components that we will endeavour to consider in costing. The costs related to the implementation of policy changes are considered from the retailer perspective. The retailer cost components will include administrative costs related to obtaining permission for later trading hours and the costs to manage and operate premises during these later hours, including staff salaries, venue maintenance and other associated costs. Due to a lack of data, we are unable to estimate costs for all venues from the retailer perspective. However, evidence from the qualitative studies (two qualitative studies were designed within the ELEPHANT study to understand the policy changes at system level and at venue level) and published sources will be used.

#### Consequences

The economic evaluation will incorporate a number of multisectoral consequences (which can also be thought of as costs/cost savings), including not only to the health service but also the judicial system. The outcomes (consequences) of this study were chosen based on the common alcohol-related harms and outcomes considered in the earlier literature to measure the impact of later trading hours. The primary outcome (consequence) will be alcohol-related ambulance call-outs (table 1). We will collect time series data from the Scottish Ambulance Service for recorded ambulance call-outs in Scotland. The available recorded electronic data on ambulance call-outs include the number of call-outs with date and time, age group, gender and council name. Using a previously developed algorithm, we will then determine which recorded ambulance call-outs are alcohol-related.^31^ To precisely evaluate the effect of the two policies regarding later trading hours for bars and clubs in Glasgow and Aberdeen, we will analyse alcohol-related ambulance call-outs that occurred throughout the weekend night-time (ie, from Friday, 20.00 to Saturday, 6.00 and Saturday 20.00 to Sunday 6.00). In addition, we will analyse all weekend night-time ambulance call-outs and reported crimes as secondary consequences (table 1). Anonymised individual data on reported crimes will be obtained from the Police Scotland IT system. We will use the Scottish Government Justice Directorate crime codes to identify crimes likely linked to alcohol consumption. This dataset will contain types of crimes with date and time, location, etc. Due to a lack of available data, we are not able to measure costs for alcohol-related road-traffic accidents, productivity losses due to alcohol-related harms (ie, reduced workforce participation due to sickness, reduced household labour due to sickness, reduced workforce and household labour due to premature mortality), increased profit for retailers due to later trading hours and increased pleasure for consumers due to additional time for social interaction.

Social service sector (third sector) costs include expenses incurred by voluntary organisations engaged in the NTE, such as volunteer training, medical kits and paramedic services. Consumers’ additional costs during the expanded hours include costs on alcohol, food and other items. Findings from qualitative studies and secondary sources, such as the websites of voluntary organisations, will be used to identify, measure and value the costs to the social service sectors. However, due to a lack of available data, we will not be able to measure the additional costs to consumers during the later trading hours.

Different cost components from multiple sectors are also associated with the primary (alcohol-related ambulance call-outs) and secondary outcomes (all ambulance call-outs and reported crimes). Alcohol-related ambulance call-outs are associated with the costs of major alcohol-related healthcare services including alcohol-related hospital admission, alcohol-related emergency services and ambulance service cost. Costs associated with reported crimes relate to three main cost areas: costs in anticipation of crime, costs as a consequence of crime and costs in response to crime.^64^ The costs of ambulance services and alcohol-related healthcare services will be measured using existing national Information Services Division (ISD) Scottish Health Service cost data. The ISD data will provide the unit cost of each alcohol-related ambulance service, as well as the cost of any subsequent health service utilisation. We will collect ambulance call-out data and whether these call-outs conveyed to hospital or not. If conveyed to the hospital, this will incur costs for the A&E department along with the cost of ambulance services. If an ambulance call does not convey to hospital, this will incur only the cost of ambulance services. Further, we will explore existing evidence from the literature on the percentage of alcohol-related ambulance call-outs that necessitate hospitalisation. Otherwise, we will analyse the costs within the A&E department only due to lack of data to link ambulance call-outs with hospitalisation and will incorporate them into the scenarios analysis. The unit cost for the reported crimes will be adopted from published sources, for example, ‘the economic and social costs of crime’.^64^

#### Perspectives

The base-case analysis (CEA) will be conducted from an National Health Service (NHS) perspective.^58^ We will identify, measure and value the cost of ambulance services, emergency services and hospitalisation services to inform decision makers with a particular focus on the health sector (table 1). The later trading hours may not only impact health services, but may increase criminal justice system costs.^35 36^ Hence, in line with the array of health and non-health sectors consequences, the CCA will incorporate health services, the criminal justice system and societal perspectives. In addition, in the sensitivity analysis, retailers’ and third sector organisations’ perspectives will be incorporated into the societal perspective.

### Economic data analysis

#### Analysis of costs and consequences

The economic evaluation will be conducted separately for Glasgow and Aberdeen. First, we will evaluate the impact of policy changes on harms, then we will conduct a CEA, cost analysis and CCA. Regression methods will be used to estimate effectiveness, that is, the impact of policy changes in Aberdeen and Glasgow. We will fit autoregressive integrated moving average (ARIMA) models with the weekly total counts for the primary and secondary consequences to assess the impact of policy changes (table 1). Such models account for autocorrelation and underlying temporal trends, and we will use Akaike information criterion and Bayesian information criterion to determine the best fitting ARIMA models. After a best fitting model is determined, we will then add the intervention variables to measure the effect size (impact of policy changes).

We will assess whether changes in the primary outcome (alcohol-related ambulance call-outs) have been caused by later trading hours. Where fewer or greater numbers of alcohol-related ambulance call-outs are found to have resulted from the policy changes, the unit cost of each resource will be multiplied by the absolute number of fewer or additional outcomes/consequences, for each city, before and after the policy changes.

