### Comparators

This study examines the impact of policy changes on outcomes and costs that are sensitive to both observed and unobserved confounding effects, due to the non-randomised study design. Therefore, based on the analysis of effectiveness, we will implement a control ITS study design (if we find a suitable control group). Economic evaluation methods also need to adapt to the challenges associated with non-randomisation and select an appropriate control group that closely approximates the intervention cities (Glasgow and Aberdeen). The objective of the control in an ITS study is to minimise biases caused by time-varying confounders, seasonality or other events that occurred during the implementation of policy changes.^52^ In this study, we will use a location-based control if we can identify any appropriate candidates. In a location-based control, different geographical areas with similar features, where the policy or intervention has not been adopted, are typically chosen. The process of suitable control selection and corresponding study design has been outlined in the flow diagram (figure 2).

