**Figure 2 F2:**
[figure not shown]
Flow diagram for the control selection procedure.

In this study, we will assess the appropriateness of the 30 Scottish councils/cities (except intervention cities—Aberdeen and Glasgow) as potential controls. No policy changes that were comparable to those in Aberdeen and Glasgow took place during our initial assessment. Later trading hours were temporarily changed for holidays (eg, Christmas and New Year), but we expect that intervention cities were similarly impacted. The appropriateness of the potential control candidates will be tested by visually and statistically assessing the assumption of parallel trends.^59^ Graphically, we will observe the preintervention differences between the intervention and control groups. If the parallel test assumption holds, then the preintervention differences will be constant over time. There are no formal statistical tests for this assumption, and passing the parallel test does not necessarily mean that the parallel trend is true.^59^ However, failing the parallel tests will make the parallel trends assumption less plausible.

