If none of the potential control candidates satisfy the parallel trends assumption, we will proceed with an uncontrolled ITS study design (figure 2). In addition, we will construct a synthetic control based on all potential control candidates since synthetic control does not need to satisfy parallel trends and will proceed with a controlled ITS study design.^60^ The synthetic control method (SCM) is widely recommended for ITS designs where multiple prospective control groups are available.^52 61^ The SCM is a data-driven process that builds a control series by calculating a weighted average of potential controls.^61^ To generate weights for the SCM, we will collect data from all Scottish councils/cities in addition to Glasgow and Aberdeen. The weights will be generated based on pre-intervention outcomes of potential control groups so that the preintervention trend of synthetic control matches well with the intervention. This process will be followed twice to generate synthetic controls for Aberdeen and Glasgow. Along with preintervention outcomes, other covariates representing time-varying confounding such as per capita gross disposable household income,^62^ number of alcohol premises/population-adjusted alcohol premises^63^ and weather (mean temperature and rainfall from the Centre for Environmental Data Analysis archive) will be used to generate weights for the synthetic control. In order to determine more accurate weights for the synthetic control series, we will incorporate population size-adjusted alcohol-related ambulance call-out and reported crimes rates for all regions in Scotland. We anticipate that, by using population-adjusted rates, the SCM series will yield a closer match to the observed outcomes prior to the intervention.

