If at least one candidate satisfies the parallel trends assumption, we will assess the qualitative and quantitative evidence on control group suitability. For example, we will qualitatively assess whether other policy changes similar to later hours occurred at the selected control cities after our initial assessment through reviewing published reports, which might limit their suitability. In addition, we will consider on-premises outlet density per 1000 population, socioeconomic and geographical features to match with the intervention context. If potential controls only satisfy the parallel trends assumption but did not get support from the qualitative and quantitative assessment, we will proceed with an uncontrolled ITS study design. However, if only one candidate satisfies both parallel trends assumption and is supported by further evidence, we will proceed with a controlled ITS study design. We will calculate mean squared prediction errors (MSPEs) for each of them, if more than one candidate satisfies both the parallel trends assumption and has favourable qualitative and quantitative evidence support. If we get only one smallest MSPE with a clear differential to other values, we will use that corresponding control and proceed with a controlled ITS study design. In addition, we will construct a synthetic control based on the selected control groups and will proceed with a controlled ITS study design based on the synthetic control. However, if there are more than one similar smallest MSPEs (ie, two or more very close MSPEs), we will select the most suitable control qualitatively and will proceed with a controlled ITS study design based on the corresponding control. We will also construct synthetic control by incorporating selected control candidates and proceed only with a controlled ITS study design.

We will assess whether any such preintervention and postintervention changes are likely to be caused by the intervention, by analysing the data for the suitable control (if any). We will use a difference-in-difference approach, such that differences between intervention and control will be used as outcome variables for both primary and secondary outcomes.

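### The article states weekly counts for the outcome model and population rates for the synthetic weights without reconciling them; unscaled count differences would let shared post-policy shocks into the costed effect

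*Protocol article*

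**What the plan says.** Four statements in the protocol article bear on scale.

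- **Outcome model** (Analysis of costs and consequences): "We will fit autoregressive integrated moving average (ARIMA) models with the weekly total counts for the primary and secondary consequences".
- **How the control enters** (end of Comparators): "differences between intervention and control will be used as outcome variables for both primary and secondary outcomes". No scale is attached to the difference.
- **Synthetic control weights** (Comparators): "we will incorporate population size-adjusted alcohol-related ambulance call-out and reported crimes rates for all regions in Scotland". The reason given is that "by using population-adjusted rates, the SCM series will yield a closer match to the observed outcomes prior to the intervention".
- **Parallel trends for location-based controls** (Comparators): "If the parallel test assumption holds, then the preintervention differences will be constant over time". This is an additive criterion, and whether it applies to counts or rates is not stated.

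The purpose of the control is to "minimise biases caused by time-varying confounders, seasonality or other events that occurred during the implementation of policy changes". Under Analysis of costs and consequences, the estimated change enters the costing as an absolute number of events times a unit cost.

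**The concern.** Counts are the only scale stated for the modelled outcome, and the modelled outcome in a controlled analysis is a difference between areas. The candidate controls are 30 Scottish councils or cities, which need not be of similar size to Glasgow or Aberdeen. The authors recognise that size matters, because they adjust for population when setting the synthetic weights, but that adjustment is not carried into the differenced outcome or into the location-based control.

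Events that act in proportion to volume have a larger absolute size in the larger area, so subtracting unscaled counts does not cancel them. If such an event falls at or after the policy date, what remains looks like a policy effect. It is then multiplied by unit costs, so the economic result carries the same error.

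**Working it through.** The article gives no effect size, sample size or control level, so there is no figure to reproduce. The check is algebra, followed by a simulation on assumed inputs.

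**Algebra.** Let the city's baseline weekly count be μ and the control's be rμ. Suppose there is no policy effect and both change by the proportion g.

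- Difference before: μ − rμ = (1 − r)μ.
- Difference after: (1 − r)μ(1 + g).
- False effect: (1 − r)gμ, that is, (1 − r)g of the city's baseline.

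With the control multiplied by 1/r, the difference is 0 before and after. On the log scale it is −log r before and after. The false effect is zero in both cases. On a rate-per-population scale the same formula applies with r read as the ratio of rates per head, so the residual is zero when those rates agree.

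**Numbers (r and g both assumed), as a percentage of the city's baseline.**

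| r | g = 5% | g = 10% | g = 20% |
|---|---|---|---|
| 0.1 | 4.5 | 9.0 | 18.0 |
| 0.5 | 2.5 | 5.0 | 10.0 |
| 0.8 | 1.0 | 2.0 | 4.0 |
| 1 | 0 | 0 | 0 |
| 2 | −5.0 | −10.0 | −20.0 |

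A shared fall reverses every sign.

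**A shock confined to the post-policy period.** The data run from 2015 to 2022 (Time horizon). The Glasgow change dates from 12 April 2019, and the article reports that the pandemic closed all nightclubs and bars (The policy changes). As an assumed illustration, take a 50% shared fall over 25% of post-policy weeks and r = 0.5, with simple averaging over the post-policy period. The result is (1 − 0.5) × 0.25 × (−50%) = −6.25% of baseline, a false reduction.

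**Simulation.** Assumptions: Poisson counts, city baseline 100 per week, 260 weeks, policy at week 200, AR(1) regression with a step and linear time, no true effect, r = 0.32, 100 runs per case. The value 0.32 is the ratio of outlets in the two intervention cities (430/1350). It only illustrates unequal size and is not a pairing the plan could use.

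| Shared change of 10% | Scale of difference | Mean false step | Declared significant |
|---|---|---|---|
| Step at policy date | counts | +6.8 call-outs | about 80% |
| Step at policy date | control rescaled | +0.2 call-outs | about 5% |
| Step at policy date | log | about 0 | about 5% |
| Linear trend, 10% of baseline per year | counts | −0.5 call-outs | about 12% |
| Seasonal cycle | counts | +1.9 call-outs | about 6% |

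The +6.8 agrees with (1 − 0.32) × 10% × 100 = 6.8. The trend case gave about 12% on the rate scale too, so that excess is not due to the count scale. With r = 1 the step case gave −0.2 and about 4%. Some fits gave convergence warnings and there are only 100 runs per case, so the rejection rates are approximate.

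**The case against.** **Differencing of raw counts is not stated.** The difference has no scale attached, and the sentence on counts also has to serve the uncontrolled interrupted time series, where counts are coherent. Rescaling is not excluded. This stands: the leak is conditional on unscaled counts being differenced. Yet counts are the only scale given for these outcomes, and a reader following the article would difference them.

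**A reader might infer that a city count is to be compared with a synthetic rate.** The article plans no such comparison. Rates are mentioned for determining the weights, and a synthetic rate can be turned into a count by multiplying by the city's population. Nor are rates stated for the location-based control.

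**A reader might infer that every shared proportional change becomes a policy effect.** That is too strong. The leak vanishes when levels match or the control is rescaled. Steady trends and regular seasonality are present before the policy and are largely absorbed by the model. Shared seasonality in the difference is |1 − r| times the city's own, so it is smaller than in the uncontrolled series for any r between 0 and 2.

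**Control selection screens out bad matches.** If raw counts are used, a council of very different size that shares proportional movements would tend to fail the constant-difference criterion. This is partly right, but the screen looks only at the pre-policy period and cannot catch a shock that comes later. It could also reject a control that would be good on a rate or log scale.

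**The analysis plan may settle it.** The article points to a preprint plan, not shown here, for more on control selection, and silence alone would be no finding. Here, however, the article does state a scale, and differencing on that scale performs worse than on a population-adjusted one.

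**Conclusion.** The point holds in conditional form. The article gives counts for the model, differences for the outcome and rates for the synthetic weights, and does not reconcile them. If unscaled counts are differenced, a shared proportional change at or after the policy date leaves (1 − r)g of the city's baseline in the estimate, and so in the costs. Across r from 0.1 to 2 with g = 10%, that runs from +9% to −10%.

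This rests on three assumptions: shared shocks act in proportion to volume, the control's level differs from the city's, and the affected weeks stay in the analysis. The article supplies neither r nor g, so the actual size is unknown. The uncontrolled branch forms no difference and is unaffected. The documents do not support saying that the planned estimate is biased by a known amount, or that the whole design is incoherent.

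**What to change.** In Comparators and in Analysis of costs and consequences, name one population-adjusted scale and use it in every controlled analysis: for the parallel-trends assessment, the mean squared prediction error, the synthetic weights and the differenced ARIMA outcome. Two forms are acceptable:

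- **Rates per population**, equivalently the control rescaled to the intervention city's population. These convert directly to absolute numbers, but cancel shared shocks fully only when rates per head are similar.
- **Log rates**, which cancel shared proportional shocks whatever the level, and need a back-transformation.

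Then state how the effect is converted to absolute call-outs and crimes for costing: multiply a rate difference by the city's population, or apply a rate ratio to the city's counterfactual count. Counts can stay for the uncontrolled analysis.

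No new data are needed beyond the population figures already required for the synthetic weights. The cost is a few sentences, a back-conversion step and, if logs are used, a rule for zero weeks in small councils or subgroups.

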#### Subgroup analysis

We will also explore impacts on different groups (men/women, age-groups, socioeconomic deprivation, based on the Scottish Index of Multiple Deprivation quintile scores on a scale of 1–5, where 1 is regarded as most deprived areas and 5 is least deprived areas). We will estimate incremental/decreased alcohol-related ambulance call-outs by available subgroups and then compute total cost to determine the economic impact of later trading hours for bars and clubs on different groups.

#### Time horizon

Deciding the time horizon for an economic evaluation is crucial and usually guided by the periods used to measure costs and consequences.^65^ Data for the primary (alcohol-related ambulance call-outs) and secondary consequences (all ambulance call-outs and reported crimes) will be collected from 2015 to 2022 to assess the impact of policy changes. The policy changes began in 2017 in Aberdeen and in 2019 in Glasgow. The most recently available cost data (unit costs) will be collected, expressed in pounds sterling (£), and if necessary, inflated for the different years using the Health Services index. All costs and consequences will be reported within an annual cycle, so there will be no need to apply discounting.

